## Abstract

**Background:**

Over 180,000 people use crack cocaine in England, yet provision of smoking equipment to support safer crack use is prohibited under UK law. Pipes used for crack cocaine smoking are often homemade and/or in short supply, leading to pipe sharing and injuries from use of unsafe materials. This increases risk of viral infection and respiratory harm among a marginalised underserved population. International evaluations suggest crack pipe supply leads to sustained reductions in pipe sharing and use of homemade equipment; increased health risk awareness; improved service access; reduction in injecting and crack-related health problems. In this paper, we introduce the protocol for the NIHR-funded SIPP (Safe inhalation pipe provision) project and discuss implications for impact.

**Methods:**

The SIPP study will develop, implement and evaluate a crack smoking equipment and training intervention to be distributed through peer networks and specialist drug services in England. Study components comprise: (1) peer-network capacity building and co-production; (2) a pre- and post-intervention survey at intervention and non-equivalent control sites; (3) a mixed-method process evaluation; and (4) an economic evaluation. Participant eligibility criteria are use of crack within the past 28 days, with a survey sample of ~ 740 for each impact evaluation survey point and ~ 40 for qualitative process evaluation interviews. Our primary outcome measure is pipe sharing within the past 28 days, with secondary outcomes pertaining to use of homemade pipes, service engagement, injecting practice and acute health harms.

**Anticipated impact:**

SIPP aims to reduce crack use risk practices and associated health harms; including through increasing crack harm reduction awareness among service providers and peers. Implementation has only been possible with local police approvals. Our goal is to generate an evidence base to inform review of the legislation prohibiting crack pipe supply in the UK. This holds potential to transform harm reduction service provision and engagement nationally.

**Conclusion:**

People who smoke crack cocaine in England currently have little reason to engage with harm reduction and drug services. Little is known about this growing population. This study will provide insight into population characteristics, unmet need and the case for legislative reform.

*Trial registration***:** ISRCTN12541454 https://doi.org/10.1186/ISRCTN12541454

## Background

The use of crack cocaine, either via inhalation or injection, is associated with adverse health and social outcomes, such as infectious disease, respiratory harms, premature mortality, acquisitive crime engagement and incarceration [1–6]. England has the highest prevalence of crack use in the European Region [7]. The population of people who use crack (PWUC) is growing, with an 8.5% rise from an estimated 166,640 in 2012 to 180,748 in 2017 [8]. An official inquiry into this increase highlights it as a serious public health concern, calling for “research to explore the characteristics of ‘hidden’ crack users who are not currently in treatment” [5]. In England, most of what is known about crack use is drawn from drug treatment and criminal justice services, and thus mostly relates to people who also inject heroin, access services for opioid substitution therapy (OST) and/or are in contact with the criminal justice system [9]. Modelling data from 2017 estimated that 29% of people who use crack in England (52,677) do not use heroin or OST and are thus less likely to be in touch with specialist drug services [8].

Provision of OST and needle and syringe programmes (NSP) are evidenced lifesaving interventions that directly benefit those receiving them by reducing risk, such as hepatitis C virus (HCV) and HIV transmission [10], but also provide indirect benefits, through facilitating links to health and social care services. While OST offers protection against heroin withdrawal, there is no commensurate pharmaceutical treatment available for crack cocaine use or dependency. Psychological treatment for cocaine dependence is advocated [11], yet motivation to engage with services can be low [5, 12]. This is particularly the case for people who smoke crack cocaine, given that in the UK provision of equipment to facilitate safer crack smoking practices is prohibited under the Sect. 9A of the Misuse of Drugs Act, 1971 [13].

There is a growing body of evidence showing associations between crack smoking and HIV and HCV acquisition, attributed to sharing of pipes [1, 2, 14–17]. Provision of injecting equipment in isolation from pipe provision, may support the choice of injection as the mode of crack administration [18]. Crack injection, often in combination with heroin, is common in England and Wales, with 54% of people who inject drugs reporting recent crack injection in 2020–21 [19]. Crack injection is associated with elevated blood-borne virus (HCV, HIV) and bacterial infection risk, given increased injection frequency compared to opioid use [20, 21]. In England, pipes used for smoking crack are often homemade or repurposed [12]. Depending on the materials employed, this can heighten risk of respiratory harm from fume and particulate inhalation with long term sequalae such as chronic obstructive pulmonary disease (COPD) as well as acute cuts and burns from using sharp or broken implements [22–26]. This in turn can increase blood-borne virus transmission risk [16].

International evidence indicates that crack pipe supply through harm reduction and drug treatment services can reduce injecting, acute injuries, respiratory harms and viral infections, and engage people with drug treatment services where health, harm reduction, and psychological interventions can be delivered [1, 2, 18, 27–32]. The quality of this body of work is limited, with a small number of published studies, of methodological heterogeneity and primarily composing observational and uncontrolled designs. Most of this work originates from Canada, where crack pipe provision is legal, and contextual differences mean that findings might not be transferable. Given prohibitions on crack pipe supply, there is a dearth of evidence on associated interventions in the UK context, although reports from Ireland, where crack pipe provision is legal, demonstrate strong intervention engagement and acceptability among highly marginalised and at-risk populations [33].

In this paper, we introduce the National Institute for Health and Care Research (NIHR)-funded SIPP (Safe inhalation pipe provision) study, which commenced in July 2022 and will run until February 2025. We provide the study protocol and discuss implications for impact. To our knowledge, this study is the first of its kind globally and has been designed to meet a pressing need in the UK context, given increasing use of crack cocaine and the high prevalence of COPD among people who smoke crack and/or heroin [23, 34–36]. Alert to the heightened risk of pipe sharing and unsafe equipment use for people with respiratory vulnerabilities, members of the study team advocated for a relaxation of restrictions to allow for crack pipe provision during the COVID-19 pandemic. This application, for a government supported memorandum of understanding between police and providers, was unsuccessful due to concerns about promotion of crack use and a dearth of UK evidence [12]. The SIPP study was designed to address these concerns, with a methodologically rigorous pre- and post-intervention survey component with non-equivalent control sites, complemented by a process evaluation and peer research capacity building in geographically diverse sites, as outlined below. Our study is designed to answer the question: “To what extent and how does SIPP reduce health risks and enhance service engagement among people who use crack cocaine?”.

### The SIPP study

The SIPP study is a mixed-method evaluation of an intervention to distribute crack equipment and harm reduction information, through specialist services for people who use drugs (e.g. NSPs, sex worker services, and other harm reduction interventions) and peer networks in England. The aim of the intervention is to reduce crack smoking risk practices and associated health harms, including through increasing harm reduction knowledge and confidence among drug treatment service providers and peers. Our goal is to reduce health and service access inequity among people who use crack, by building an evidence base to inform service provision and promote review of the legislation prohibiting crack pipe supply. Our proposed pathway to achieve change is outlined below (Fig. 1).

**Fig. 1 Fig1:**
[figure not shown]
SIPP logic model

We employ a mixed-methods quasi-experimental design to examine whether, to what extent and how SIPP acts to reduce health risks and enhance service engagement among people who use crack cocaine. Objectives, detailed in Table 1, will be achieved through the implementation of: (1) peer-network capacity building and co-production; (2) an impact evaluation comprising a pre- and post-intervention survey with a non-equivalent control group; (3) a process evaluation comprising ethnographic observations, qualitative interviews and monitoring data; (4) an economic evaluation. Detail on each study component is provided below, after a brief outline of the SIPP intervention and study sites.

**Table 1 Tab1:** SIPP study objectives and components

SIPP objective	Study component
1. Build peer-network research capacity and explore whether the quality and impact of their SIPP engagement with PWUC differs in comparison with SIPP engagement through drug treatment services	Peer network
	Process evaluation; Impact evaluation
2. Measure the effect and cost-effectiveness of the SIPP kit on harms and risks associated with crack use (pipe sharing, presentation at drug services, using homemade pipes, cuts/burns, crack injecting)	Impact evaluation; economic evaluation
3. Evaluate SIPP fidelity, reach and acceptability in diverse specialist drug service and peer-network settings	Process evaluation
4. Explore the barriers and facilitators to SIPP uptake and service engagement among PWUC	Process evaluation
5. Explore the mechanisms through which SIPP facilitates changes in health risks and access to services, and how these are shaped by local contextual factors	Process evaluation
6. Co-develop a scalable SIPP toolkit and harm reduction resources to enhance PWUC engagement with specialist drug services and to facilitate crack-related risk reduction practices	Peer network
7. Translate evidence to policy and advocacy outputs, including to inform legislative review	All components

### The SIPP intervention

SIPP is a structural intervention. That is, an intervention that promotes the availability, accessibility or acceptability of specific resources needed for specific health outcomes [37]. It is informed by comparable interventions, harm reduction principles and models of community mobilisation evidenced to have impact in diverse contexts [38, 39]. The SIPP intervention was co-produced by the team with input from people who use crack and service providers and will be delivered at study intervention sites for a period of six months.

It consists of three components:The SIPP KIT: The SIPP kit adheres to best practice guidance for provision of safe crack inhalation equipment [32]. It comprises a straight stem borosilicate glass pipe; 2 × steel gauze filters/meshes; 2 × plastic mouth pieces; and a wooden push stick, contained within a discrete hard plastic case. A brief harm reduction leaflet with instructions and a card providing information about the research study are provided with each kit (see Fig. 2)SIPP Provider Training: Informed by an evidence review, workshops with providers of specialist services for people who use drugs, and peer/stakeholder review, we developed an online training module aimed at service providers. This provides background information on crack (drug properties, use in the UK context); associated health harms and harm reduction advice; homemade pipes, suspension devices (ash, wire wool) and risk; client engagement tips; SIPP kit use and provision. Training evaluation and participant registration details are embedded within the platform.Peer-2-peer harm reduction: Brief verbal harm reduction messaging to support SIPP kit provision. With peers (i.e. people who use crack) we developed a hierarchy of harm reduction messages that can be tailored to suit an individual's specific information requirements and time available. The development and provision of this messaging is an iterative process, informed by feedback from peer researchers on local participant needs and contexts of delivery.

**Fig. 2 Fig2:**
[figure not shown]
SIPP Kit

### Study partners and sites

The SIPP study would not be possible without the support of local police forces, specialist drug service providers, community members and charity organisations working to support peer advocacy and involvement. Prohibition of crack pipe provision necessitated contact with local Chief Constables and Police and Crime Commissioners prior to study site selection. Our intervention sites in Bristol, Nottingham, and Mansfield, are under the jurisdiction of the Avon & Somerset Police and the Nottinghamshire Police, respectively. Both have provided written approval for SIPP kit distribution through our specialist drug service providers and peer-network partners for the six-month duration of the intervention.

Non-equivalent control sites have been selected for intervention site comparability, with attention to local geography, demographics and the number of people using specialist services for drug use type recorded as using crack cocaine. Geographical distance between control and intervention sites decreases contamination risk. The control sites are: Birmingham (for Bristol, conurbations); Coventry (for Nottingham, mid-sized cities); Leamington Spa and Nuneaton in Warwickshire (for Mansfield, Nottinghamshire, peri-rural/rural sites adjoining Coventry and Nottingham, respectively). Each intervention and control site has a primary partner who is specialist provider of services for people who use drugs, with additional peer network and outreach distribution supported by Coact (Bristol), The Hepatitis C Trust (Birmingham) and POW sex worker support service and outreach (Nottingham). See Table 2, below.

**Table 2 Tab2:** Intervention and non-equivalent control sites

Service type	Intervention site	Non-equivalent control site
Specialist drug service	Nottingham Health Shop/Well-being Hub	Change Grow Live—Coventry
Sex worker support service	POW Nottingham	
Specialist drug service	Bristol Drugs Project	Change Grow Live—Birmingham west
Peer network	Bristol COACT peer activist group	Hepatitis C Trust peer outreach—Birmingham
Specialist drug service	Change Grow Live –Nottinghamshire	Change Grow Live—Warwickshire

### Study population

Our study population for the evaluation are people who use crack cocaine, defined as people who self-report smoking or injecting crack in the past 28 days. To participate they must be aged 18 years or over and have the capacity to consent. Excluded are those aged under 18 years; currently incarcerated; lacking capacity for informed consent; or with no history of crack use. We include people who inject crack as a SIPP target population, given the potential for inhalation equipment provision to support transitions from injection and reduce injection frequency.

### Ethical issues

Ethical approval has been granted by The London School of Hygiene & Tropical Medicine (LSHTM) Research Ethics Committee (REF: 28102). Consultation has taken place with specialist drug service providers, their clients and organisations representing people who use drugs to ascertain that the project design does not place any undue burden or risk on potential participants. The co-production of the intervention with people who use crack and the embedded role of peers throughout, including as members of the research team and advisory board, helps to ensure that the project is acceptable and accountable to the communities involved.

Prior to project commencement the team will provide staff and volunteers at the specialist drug services training in research methods, with emphasis on prioritising the confidentiality and autonomy of people from marginalised and criminalised populations. All services have been provided with a list of local health and social support services to ensure a range of support options to participants where needed. All participants will be informed of what will happen to their data and measures taken to ensure confidentiality, prior to providing consent. De-identified qualitative interview transcripts will be encrypted and stored on password-protected LSHTM computers. Audio files will be destroyed once transcribed. All questionnaire data will be collected via the Open Data Kit software (ODK collect) on handheld password-protected tablet devices. Once each questionnaire is finalised, ODK Connect applies an asymmetric public key encryption using 256-bit encryption, which is irreversible and ensures that the finalised questionnaire data are not readable and are not tampered with. The encrypted form is sent to a central server hosted at LSHTM and downloaded to a secure server by the team data manager.

The safety of peers and providers engaged in the intervention delivery is paramount. Intervention police forces have provided written assurance that our specified peers and providers are exempt from prosecution for crack pipe supply. The team have met with and provided training to one police force, in particular, who have also nominated to provide peers with additional protection through the development of police approved identification badges including a study specific code which will inform concerned officers of the study remit and exemptions from prosecution. All peers involved in the project receive training in research methods and regular debriefs and check-ins with the qualitative research team. Throughout, it is stressed that peer safety and well-being take prominence over data generation and if a peer wishes to cease or change their role they will be supported to do so.

The ethics of intervention cessation are a concern, particularly if crack pipe provision is found to be highly valued and associated with positive outcomes for people who use crack. We have put in place measures to manage expectations of provision, including a card to be provided with each SIPP kit and posters to be displayed prominently in services. Both highlight that SIPP crack pipe provision is a time limited intervention, taking place as part of a research study. Although SIPP is not a clinical intervention, participant experiences in heroin-assisted therapy trials such as SALOME and NAOMI in Canada [40] demonstrate the need for caution. Here, the lack of an appropriate exit strategy meant that participants who experienced life-changing benefits from heroin-assisted therapy were required, at the end of the trial, to return to conventional treatments that had previously failed them. In response the SALOME/NAOMI Association of Patients filed a Supreme Court constitutional challenge to the trial discontinuation procedures, as part of their advocacy for treatment continuation [40]. Although not of the same magnitude, the potential for crack pipe provision to offer an avenue for meaningful service engagement and/or reduce risk practices and acute health harms, poses ethical concerns regarding intervention cessation. This is further complicated by the legal status of provision, with police approvals only in place for the intervention duration.

### Study components

#### 1. Peer capacity building and co-production

Community mobilisation and capacity building are central to the SIPP project design. We adopt a multi-pronged recruitment approach, working with community-based specialist services for people who use drugs but also peer activists and networks who are experienced in delivering harm reduction interventions to their communities. Through a dynamic process of peer researcher development and community mobilisation we will capacitate and evaluate peer-led provision of the SIPP intervention alongside provision through more traditional harm reduction services. Peers (i.e. people with past and/or present experience of crack use) in three sites (Bristol, Nottingham and Birmingham) will receive training in research methods, including those specific to SIPP, and be supported by the team to deliver each study component as appropriate to their location (intervention/control). At each site, 3–5 peers will generate pre- and post-survey data with a focus on recruiting people not accessing drug treatment services, women, and ethnic minorities. During the six-month intervention period peers in the intervention sites will distribute pipes and harm reduction advice, with a focus on reaching the underserved communities recruited during survey generation. All peer researchers will be remunerated for their time and expenses, including for training participation.

People who use crack have privileged access to the communities in which they live. Our peer-network team members provide unprecedented access to people who use crack who are not in touch with services. Peers are instrumental in transferring crack risk reduction knowledge [38] and providing support in the context of drug use, homelessness and exclusion [39, 41]. This project will add value by seeking to understand the barriers and facilitators to working with peer networks as research partners to inform future community-participatory research with marginalised populations. In addition, we will explore if the mode of SIPP delivery (peer network vs. drug treatment service) influences SIPP acceptability and reduction in risk practices. This knowledge has transferable value to inform scale up of other harm reduction and public health interventions for marginalised populations (NSP, vaccine rollout, etc.).

The team have extensive experience of working with community members including to build research capacity, and to develop peer-led harm reduction initiatives in contexts of service constraint and inaccessibility. The study principal investigator and two SIPP co-investigators have past & present experience of crack use. We have drawn on their connections to work closely with peers throughout the development of this proposal to arrive at an implementation and evaluation design that is feasible and acceptable to peer researchers, including in regard to modes of recruitment, data collection devices, training needs, reimbursements provided and control measures. In addition, the specialist services for people who use drugs in each site have been provided with funding to employ a service user or early career staff member with lived experience to administer the pre- and post-intervention survey. This reduces drug treatment staff burden and capacitates a local peer volunteer in research methods. Findings will be regularly fed back to and interpretation discussed with peer researchers and their networks, including through analysis, resource development and dissemination workshops.

#### 2. Impact evaluation

We will implement a pre-post-intervention survey at the intervention and control sites to measure the impact of SIPP on our primary and secondary outcomes. The survey will run for 10 weeks either side of the six-month intervention period and will be administered by trained staff and peers at each specialist service for people who use drugs, and through peer-network outreach in Bristol, Nottingham and Birmingham.

##### Data collection

Two surveys will be conducted six months apart to allow for the intervention phase. For both the pre- and post-survey, a structured questionnaire will be administered by staff at specialist drug services and peer researchers, trained in data collection methods, informed consent procedures and all aspects of the study protocol. Service providers and peers will approach potential participants and current clients, describe the study and discuss contents of the information sheet and consent form. Participants who consent will complete a structured questionnaire in English on a Lenovo tablet device with the ODK collect app either self-completed or administered by a service provider or peer. The questionnaire takes approximately 30 min to complete and contains the follow sections: demographics (including age, gender identity, sexual orientation, ethnicity, and source(s) of income); drug use practices (including drugs taken, routes of administration, and equipment sharing/reuse); indicators of social exclusion (including housing status and healthcare access); policing (including recent arrest and history of incarceration); primary and secondary outcomes (see below). Our questionnaire has been developed with input from peers and service providers and incorporates measures used in comparable surveys with people who use crack in Canada and UK [2, 18, 27, 28, 30, 42] as well as drawing on a questionnaire piloted by peers in 2020 for SIPP study conceptualisation. We will not actively follow-up participants, but we will collect minimal identifiers (date of birth, initials) needed to link people over time to allow assessment of primary and secondary outcomes and new presentations at specialist drug services. The same questionnaire will be used to collect post-intervention survey data.

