##### Outcome measures

Our primary outcome measure is a decrease in the proportion of participants self-reporting sharing of crack pipes in the past 28 days (yes/no).

Secondary outcomes comprise:increased presentations at specialist drug services defined as: a) the change in proportion of attendances at specialist drug service sites in the past 6 months (number of new attenders in past 6 months/total number of clients) measured through data linkage to drug service records; and b) the change in proportion of participants attending a specialist drug service in the past 6 months (measured through self-report yes/no)reduction in injecting frequency defined as number of times injected in the past 28 daysreduction in number of days sharing pipes in the past 28 daysdecrease in proportion of those reporting current acute injuries defined as cuts/burns to mouth or lips in the past 28 days (yes/no)reduction in the proportion of participants who use homemade pipes in the past 28 days (yes/no)reduction in proportion of participants using ash as a crack suspension device in the past 28 days (yes/no)reduction in proportion of participants reporting respiratory risk markers defined as difficulty breathing, chest pain, coughing blood in the past 28 days (yes/no).

Our primary and most of our secondary outcomes are self-reported. Self-report measures of drug-related risk behaviours are deemed reliable, particularly when used with computer assisted survey instruments [43, 44]. The use of self-reported measures in evaluating the impact of harm reduction interventions such as NSPs is widespread [45]. Self-reported crack pipe sharing has been used as an outcome measure for Canadian studies [18, 27, 46] aiding comparability. Service presentations will be assessed through the collection of minimum identifiers (initial and date of birth) for participants in pre- and post-surveys and from each person obtaining a SIPP kit as part intervention monitoring for the process evaluation (see below). These minimum identifiers will be used to link data from surveys and SIPP monitoring, and also allow linkage of both survey and SIPP monitoring data with specialist drug services client lists before and after the intervention to review increased service presentation due to SIPP.

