##### Sample

We will interview 36–45 people who use crack across the intervention sites (12–15 per site), with interviews spanning the pre-post-survey and intervention periods. We will purposively sample for variation in gender, ethnicity and age. A smaller number of people (6–9), sampled for duration of crack use (5 + years), will be recruited at the control sites (2–3 per site) to obtain an understanding of local crack use practices and market dynamics. Peers and providers involved in delivering the SIPP survey and intervention will facilitate recruitment. Clients meeting our purposive sampling criteria will be informed of the qualitative arm of the study and provided with a participant information sheet. If interested, they or the peer/provider can facilitate research team contact. We will also interview 15–18 service providers and peer researchers involved in survey and intervention delivery across the sites and select stakeholders (police, commissioners) purposively sampled to reflect variation in relevant occupational roles (*n* = 5–8). Stakeholders will be recruited through professional networks, and peers/providers through the engagement of the research team at each site. Total qualitative interviews 62–80. Flexibility in recruitment numbers allow for theoretical sampling. This is a grounded theory technique whereby early analysis of purposively sampled participant data allows for additional targeted sampling to address analytic gaps, puzzles or leads [48].

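### Intervention-site peers both collect the survey data and hand out kits, and survey mode is left open, so under-reporting of pipe sharing to a kit supplier could look like a SIPP effect; its size is unknown

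*Protocol article*

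**What the plan says.** All the text is in the protocol article; no separate analysis plan was available.

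- **Who asks.** Under Data collection, for both surveys "a structured questionnaire will be administered by staff at specialist drug services and peer researchers". The form is "either self-completed or administered by a service provider or peer". No rule says which mode applies to whom, at which site or at which wave.
- **Peers.** Under Peer capacity building and co-production: "At each site, 3–5 peers will generate pre- and post-survey data". The same paragraph continues: "During the six-month intervention period peers in the intervention sites will distribute pipes and harm reduction advice", aimed at the communities reached during the survey.
- **Services.** Study partners and sites describes "SIPP kit distribution through our specialist drug service providers and peer-network partners". The services are also funded "to employ a service user or early career staff member with lived experience to administer the pre- and post-intervention survey".
- **Both roles together.** The process evaluation's Sample section, on recruiting interviewees, says: "Peers and providers involved in delivering the SIPP survey and intervention will facilitate recruitment".
- **Outcome.** The primary outcome is self-reported pipe sharing in the past 28 days. Outcome measures defends this: "Self-report measures of drug-related risk behaviours are deemed reliable, particularly when used with computer assisted survey instruments".
- **Numbers.** Recruitment gives 500 intervention participants (400 through services, 100 through peer networks) and 240 controls. Sample size assumes that 52% share pipes and plans for a 20-point difference.

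**The concern.** The primary outcome is an unblinded self-report. A participant who has been given pipes may be reluctant to tell the supplier that he or she still shares. A general tendency to under-report would largely cancel between groups, because all sites may use the same survey modes. Reluctance tied to the supplier would not cancel: control sites supply no kits, and at the pre-survey no one has yet received one. Such a bias would therefore have the same group-by-time pattern as a real effect. Covariate adjustment, linkage and a larger sample do not remove it.

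The other self-reported practice outcomes (days sharing, homemade pipes, ash) could be affected in the same way. The per-protocol and dose–response analyses may be more exposed, since they select or rank people by contact with SIPP. The results are meant to inform legislative review. If mode and interviewer role are not recorded, the question cannot be examined afterwards.

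**Working it through.** **1. The plan's own figure.** Inputs from Sample size: 52% v 32%, 90% power, p = 0.05, allocation 2:1. A two-sided, continuity-corrected comparison of two proportions gives 102 controls and 204 SIPP, total 306, which matches the plan exactly. Without the correction the total is 282. The sample size is not in question; the point is about bias.

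**2. Model of the bias.** Let true sharing be 52% in both groups (no effect). Let *s* be the share of the 500 intervention participants who answer to a kit supplier, and *u* the share of sharers among them who deny it at the post-survey. Then reported sharing = 0.52 × (1 − *su*), and the spurious fall = 0.52 × *su*.

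The article gives neither *s* nor *u*. I assume *u* = 10% and 20%. For *s* I use the peer-recruited group alone (100/500 = 0.2), half the sample, and all of it.

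**3. False-positive rate, post-survey only, 500 v 240.** SE = √[p(1 − p)/500 + 0.52 × 0.48/240] ≈ 0.039. The rate is P(|Z| > 1.96) when Z is centred on fall/SE.

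**4. False-positive rate, difference in differences.** Treating the two surveys as independent samples of 500 and 240, SE = √[0.2496/500 + 2 × 0.2496/240 + p(1 − p)/500] ≈ 0.055. Linked participants would change this somewhat.

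| *s* | *u* | Reported sharing | Spurious fall | Post-only | Difference in differences |
|---|---|---|---|---|---|
| 0.2 | 10% | 51.0% | 1.0 points | 5.8% | 5.4% |
| 0.2 | 20% | 49.9% | 2.1 points | 8.3% | 6.6% |
| 0.5 | 10% | 49.4% | 2.6 points | 10% | 8% |
| 0.5 | 20% | 46.8% | 5.2 points | 26% | 16% |
| 1 | 10% | 46.8% | 5.2 points | 26% | 15% to 16% |
| 1 | 20% | 41.6% | 10.4 points | 76% | 47% |

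The nominal rate is 5%. Counting only results that favour SIPP, the 5.2-point rows give 15.3% for the difference in differences; counting both directions gives 15.5%.

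**5. Against the planned effect.** 1.0 to 2.1 points is 5% to 10% of the planned 20. 5.2 to 10.4 points is 26% to 52%. To produce the whole 20 points, denial would have to reach 0.20/0.52 = 38% with everyone exposed.

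**The case against.** The strongest reply is that documented overlap covers a minority of the sample. Only the peer route has survey and supply in the same hands, and it recruits 100 of the 500. Services recruit the other 400 and are funded for a survey administrator, which the article says relieves treatment staff. Participants may also self-complete, and the primary analysis includes people who never took a kit. This stands, and it is why the exposed share must be given as a range. It does not settle the matter, because nothing says the administrator is kept apart from kit supply.

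Second, peer administration is deliberate: it reaches people outside services, and surveyors are trained in data collection and confidentiality. That also stands. The fix keeps peers as recruiters and helpers.

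Third, form fields and surveyor instructions may sit in a fuller protocol. True, but the point is the open choice of mode that the article states, not the absence of such detail.

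A reader might infer more than the text supports:

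- **That kit suppliers will interview the whole intervention sample, so 26% to 76% is the expected error rate.** Those figures need all 500 exposed and a post-only test. The article promises an estimate of change, with time and treatment effects in the model.
- **That the intervention explicitly advises against pipe sharing.** This is plausible, but the intervention description does not give such a message and the leaflet text is not shown.
- **That the defence of self-report rests on privacy.** The article gives no such reason, and its cited sources cannot be checked here.
- **That questions will be put face to face, or that the pressure exists only after the intervention and only at intervention sites.** The first is an inference from the word administered; the second is likely but assumed.

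**Conclusion.** The concern holds as a moderate, cheaply reducible risk of bias. The article puts survey collection and kit supply with the same peer group at intervention sites, allows the same for service staff, and leaves mode open for a self-reported primary outcome. Under-reporting to a supplier would probably fall mainly on intervention sites at the post-survey, where the control comparison cannot remove it.

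With 10% to 20% denial among exposed sharers, the spurious fall runs from 1.0 to 2.1 points (only the peer-recruited 100 exposed) to 5.2 to 10.4 points (all 500 exposed). The lower figures are not a floor: if the peer-recruited participants self-complete in private as well, the bias could be close to nil. The denial rates and exposed shares are assumptions, and the calculation ignores clustering by site. It shows what could happen and does not predict the result.

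**What to change.** 1. **Data collection.** Make private self-completion on the tablet the default for the outcome items (sharing, days sharing, homemade pipes, ash, injecting), at both waves and all sites. Give assistance on request and, where feasible, from someone who does not supply kits to that participant. With 3 to 5 peers per site this cannot always be met, so it should not be absolute.
2. **Form.** Record mode (self-completed or assisted) and the interviewer's role, including whether that person supplies kits.
3. **Analysis.** Add a pre-specified sensitivity analysis of the primary outcome by mode and interviewer role.
4. **Outcome measures.** Keep the statement on self-report, and add that a risk of under-reporting remains where a provider or peer administers the form.

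The cost is an instruction to surveyors, two fields on tablets already in use, and one further analysis. The downside is extra time or some missing answers among people with low literacy, who can still be assisted and would be flagged. Mode is not randomised, so the sensitivity analysis can signal a problem but cannot by itself correct for it.
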